## Sampling Techniques and Tools

Research assistants will work with clinical staff to screen and recruit ALWH from five HIV clinics in Lilongwe, Malawi. A random sample of 10 ALWH participants and a random sample 10 clinic staff involved in the delivery and/or supervision of FB+SP will be invited to participate in exit interviews to assess intervention delivery and contextual factors that impeded and facilitated implementation.

## Sample Size Determination

Trial: We expect to be able to recruit 60 ALWH. The primary goal of this R34 proposal is to evaluate the feasibility, acceptability, and fidelity of the enhanced FB+SP model to address suicidality ALWH. In Aim 2, we will enroll 60 ALWH with SIBs in a 2-arm randomized pilot (30 per arm) to compare augmented usual care with the enhanced FB+SP intervention. Information on preliminary effectiveness of the intervention across a range of mental health outcomes related to SIBs will be assessed, but interpreted cautiously as efficacy is only a secondary aim of this pilot study. Intervention effectiveness will subsequently be assessed in a large-scale R01 clinic-level RCT. The sample of 60 ALWH (30 per arm) will be sufficient to estimate quantitative measures of feasibility and acceptability with reasonable precision (e.g., standard errors of .06-.09 for proportions).

Qualitative Interviews: Some providers involved in the delivery of the FB+SP intervention (N=10) and patients in the intervention arm (N=10) will be asked to complete brief exit interviews at their study sites to assess facilitators and barriers to the delivery and receipt of the FB+SP intervention. As is common in qualitative research, we aim to continue data collection until data saturation has been achieved. Based on prior experiences employing these methods and achieving saturation, this sample size is expected to be sufficient to capture a diverse range of perspectives as well as achieve theme saturation in each group.

## Data Collection Techniques and Tool

Implementation outcomes: This trial will explore patient and provider ***acceptability*** and ascertain ***feasibility*** of recruitment, retention, and participation. We will conduct audio-recorded semi-structured qualitative interviews with a random sample of patients enrolled in the study (N = 10). Exit interviews will explore acceptability of the intervention to patients (ease of participation or delivery, perceived usefulness of the intervention, suggestions for improvement, and contextual factors that impeded or facilitated implementation). Acceptability will also be assessed quantitatively with the *Client Satisfaction Questionnaire-8*.^57^ Feasibility will be assessed through the number of ALWH enrolled; a comparison of planned relative to actual enrollment; reasons for non-enrollment; the proportion of ALWH retained in each arm; and the number of sessions attended during the study period. Additionally, we will interview clinic staff (N = 10) involved in the delivery and/or supervision of the intervention to assess acceptability to providers and feasibility (perceived changes, comfort level and competency, training satisfaction, recommendations, barriers and facilitators). We will monitor ***fidelity*** to the intervention protocol using the *Fidelity Checklist­* and in-depth interviews with clinic staff (**Table 1**).

Preliminary Effectiveness: This trial will assess patient outcomes as a measure of preliminary effectiveness, comparing the prevalence of SIBs, suicide risk, and depressive symptoms between the two study arms. Patients will be surveyed by the RAs at enrollment (baseline), 2 weeks post-enrollment (FU1), 4 weeks post-enrollment (FU2), 6 weeks post enrollment (FU3), 3 months post-enrollment (FU4), and 6 months post-enrollment (FU5) (**Table 1**). VL draws will occur at enrollment (baseline) and 6 months post-enrollment (FU5). Additionally, RS will abstract clinical data related to ART appointment attendants, providers assessment of patients’ depressive symptom and suicidal ideation and behaviors and continue treatment as clinically indicated.

| **Table 1. Assessment Domains, Constructs, and Measures** | | | | |
| --- | --- | --- | --- | --- |
| **Domain** | **Construct** | **Measures** | **Assessment Point** | **Data**  **Type** |
| **Primary Implementation Outcomes** | | | | |
|  | Feasibility | # enrolled; # planned vs. # actual enrollment; reasons for non-enrollment; % retained in each arm; # of sessions attended | Ongoing | Clinic |
|  |  | In-depth interviews | Exit Interview | Qual. |
|  | Fidelity | Checklist for content covered during sessions | Ongoing | Clinic |
|  | Acceptability | Adapted Client Satisfaction Questionnaire-8^57^ | FU1, FU2 | Survey |
|  |  | In-depth interviews | Exit Interview | Qual. |
| **Secondary Preliminary Efficacy** | | | | |
|  | SIBs | PHQ-9-A Question 9 and ASQ Tool^50,56^ | Ongoing | Clinic |
|  | Suicide Risk | Suicide Risk Assessment Protocol^17^ | Ongoing | Clinic |
|  | Depressive Symptoms | PHQ-9-A^50^ | Ongoing | Clinic |
| **Covariates & Mediators** | | | | |
|  | Demographics | Age, sex, resources, education, religion, occupation, health status, awareness of HIV status at ART initiation, home distance | BL | Survey |
|  | Disclosure | HIV and Suicidality Disclosure to Family and/or Friends | BL | Survey |
|  | MH Care Engagement | FB+SP appointment dates, other MH treatment | Ongoing | Clinic |
|  | HIV Care Engagement | ART appointment dates, ART pill count, VL draws | Ongoing | Clinic |
|  |  | VL draws | BL, FU5 | Study |
|  | HIV Stigma | Internalized AIDS-Related Stigma Scale^58^ | BL, FU3-5 | Survey |
|  | Suicide Stigma | Personalized Suicide Stigma Questionnaire^59^ | FU3-5 | Survey |
|  |  |  |  |  |
|  | Suicide Coping | Suicide Related Coping Scale^60^ | BL, FU3-5 | Survey |
|  | Isolation | Adapted Interpersonal Needs Questionnaire items^61^ | BL, FU3-5 | Survey |
|  | Burdensomeness | Adapted-Suicide Cognitions Subscale items^62^ | BL, FU3-5 | Survey |
|  | Hopelessness | Adapted-Beck Hopelessness Scale items^63,64^ | BL, FU3-5 | Survey |
|  | Acquired Capability | Adapted-Acquired Capability for Suicide Scale items^61^ | BL, FU3-5 | Survey |
|  | Sleep Quality | Pittsburgh Sleep Quality Index^65^ | BL, FU3-5 | Survey |
|  | Trauma | PC-PTSD-5^66^ | BL, FU3-5 | Survey |
|  | Alcohol/Marijuana | Single-question alcohol screening test^67^; single-item screen-cannabis.^68^ | BL, FU3-5 | Survey |
|  | Social Support | Multi-dimensional Scale of Perceived Social Support^69,70^ | BL, FU3-5 | Survey |
|  | Resilience | PLHIV Resilience Scale^71^ | BL, FU3-5 | Survey |
| **NIH Common Data Elements** | | |  |  |
|  | Anxiety, Depression, Functioning | Revised Children’s Anxiety^72^ and Depression Scale-25 (RCADS-25) Youth Assessment^73^ | BL, FU3-5 | Survey |
|  | DSM-5 Cross-cutting | DSM-5 Cross-cutting assessment Youth Self Report ^74,75^ | BL, FU3-5 | Survey |

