# METHODOLOGY

## Design of Study

In this randomized controlled pilot trial across five public health clinics, participants will be individually randomized 1:1 either to enhanced FB+SP (N = 30) or augmented usual care (N = 30) and followed for 6 months. Primary and secondary outcomes will be assessed at 2-, 4-, and 6-week; and 3- and 6- month study visits and compared across the two study arms.

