**Box 1: FB+SP Package**

Session 1 (Week 1; 45-60 min)

- SIBs & Suicide Risk Assessment

- Psychoeducation & FB+SP Introduction

- SP activities & Strategy Creation

Sessions 2 (Week 2; 40-45 min)

- SIBs & Suicide Risk Assessment

- SP Check-in & Revision

- FB Problem-Solving Initiation

Sessions 3-6 (Weeks 3-6; 15-20 min)

- SIBs & Suicide Risk Assessment

- SP Check-in & Revision

- FB Problem-Solving Continuation

Concurrent Peer-Support

- 6 group peer-support sessions

- Delivered Monthly

*Optional Ad-hoc Support*

- Telephone/text message check-ins

FB+SP: The FB+SP protocol will embed SP within the existing adolescent-friendly FB model, tailored for the Malawian context.^22,53^ The protocol will include six sessions, starting with the development of the SP during the first session (**Box 1**). Each of the following sessions will include SIBs and suicide risk assessments, SP check-ins and revisions, as well as FB problem-solving to address SIBs and suicide risk (**Box 1**). SP+FB will be delivered by selection of young counselors (mixed genders, aged 20-35) who are motivated to work with young people. Counselors will be trained to deliver non-judgmental counseling that respects the privacy and autonomy of ALWH and enables them to make free and informed choices that are relevant to their individual needs. Training will also include discussion of adolescent development and the unique experiences of ALWH related to stigma, disclosure, social relationship issues, and health care access. Counseling sessions will take place in a youth oriented but discrete location within the HIV clinic and be available on weekends to ensure accessibility.

SP will be initiated on the first session and will consist of an introduction to the program, a SIBs and suicide risk narrative assessment and the co-development of a personalized list of coping strategies. SIBs and suicide risk will continue to be assessed at follow-up sessions, with option telephone and/or text message check-ins.

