FB problem-solving counseling will begin on the second session. The first FB session includes three components called Opening the Mind, Uplifting, and Strengthening, with subsequent sessions building on the first. Opening the Mind refers to the therapeutic process by which, through asking questions, clients are encouraged to open their minds to identify their problems, choose one to work on, identify a feasible solution, and agree on an action plan through an iterative process guided by the counselor. Each structured session lasts 30-45 minutes and will be conducted in a private clinic room in the participant’s local language (Chichewa). No specific retention support will be provided, but participants may identify barriers to engagement in HIV care to address during their counseling session. After 4 sessions of individual therapy, the counselor can refer participants not improving or with suicidal ideation to a supervisor trained in mental health to reassess and manage the case. Case management may include additional counseling or pharmacotherapy, at the discretion of the managing clinician.

Additionally, adolescents will be offered structure peer support via in person group meetings to facilitate engagement in care for ALWH and support SIBS reduction, as is now standard with the existing adolescent-FB package.^53^ Peer supporters will be mature young adults (aged 18-21) who have completed secondary school, are openly living with HIV, and motivated to work with adolescents. The counselors must be willing to maintain participant and colleague confidentiality and sign a confidentiality agreement. Peer Supporters will be trained to deliver youth-friendly group sessions related to HIV care. The content of the 6 peer support sessions includes: Mental Health and HIV, Status Communication, Adherence and Viral Load Testing, Secondary Prevention (Sex and Relationships), Stigma, and Planning for the Future. The 6 sessions will be delivered monthly over 6 months and last 90 minutes each. The group sessions will be in a private space in the clinic in the participant’s local language (Chichewa).

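### The only quantitative acceptability rating (adapted CSQ-8) stops at week 4, before the last 2 counselling sessions and 5–6 of the 6 peer-support sessions

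*Protocol*

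**What the plan says.** The Sample Size Determination section puts acceptability in the main aim: "The primary goal of this R34 proposal is to evaluate the feasibility, acceptability, and fidelity of the enhanced FB+SP model". Table 1 lists it under the primary implementation outcomes with two sources. One is the adapted CSQ-8, scheduled as "Adapted Client Satisfaction Questionnaire-8^57^ | FU1, FU2 | Survey". The other is in-depth interviews at exit. The Data Collection section dates the visits: "2 weeks post-enrollment (FU1), 4 weeks post-enrollment (FU2), 6 weeks post enrollment (FU3), 3 months post-enrollment (FU4), and 6 months post-enrollment (FU5".

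The package being rated lasts longer than that. Box 1 gives six weekly counselling sessions, ending with "Sessions 3-6 (Weeks 3-6; 15-20 min", and includes "6 group peer-support sessions". The Design of Study text adds: "The 6 sessions will be delivered monthly over 6 months and last 90 minutes each".

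The Data Analysis section plans to report, for acceptability, the share of participants who judged the intervention easy and helpful. It does not name the source of that share. CSQ-8 is the only quantitative acceptability instrument the protocol names, so I take it to be the source. Nothing in the protocol schedules CSQ-8 after FU2, and no reason is given for stopping there.

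**The concern.** A satisfaction score taken at weeks 2 and 4 rates what participants have received by then. If it is reported as the acceptability of FB+SP, it will be read as covering the whole package, although most scheduled contacts come later. Dissatisfaction that arises in the last counselling sessions or in the monthly groups would not reach the quantitative score. The pilot is meant to inform a later, larger trial, so an acceptability proportion that leaves out most of peer support is a weak basis for deciding whether to keep that component. The gap cannot be repaired in analysis, because the data would never have been collected.

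The timing also stands out within Table 1. CSQ-8 is the only survey instrument placed at FU1 and FU2. The other repeated survey scales are all collected at FU3 to FU5, so later survey contacts already exist.

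**Working it through.** **1. The plan's own figure.** The Sample Size section gives standard errors of .06–.09 for feasibility and acceptability proportions. With SE = √(p(1−p)/n) at p = 0.5:
- n = 60: √(0.25/60) = 0.0645
- n = 30: √(0.25/30) = 0.0913

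The stated range reproduces. It concerns precision and says nothing about when the rating is taken.

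**2. Inputs for the timing check.**
- Visits: FU1 to FU5 at 2, 4 and 6 weeks and 3 and 6 months (Data Collection section).
- Counselling: one session per week, six in all (Box 1).
- Peer support: six sessions, monthly over six months (Box 1 and Design of Study).
- Assumptions: delivery starts at enrolment and runs on schedule, and months are calendar months (52/12 = 4.33 weeks). The first peer session is not dated, so it is placed either at enrolment or at the end of month 1.

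**3. Sessions scheduled by week w.** Counselling = min(6, w). Peer support lies between ⌊w/4.33⌋ and ⌊w/4.33⌋ + 1, capped at 6.

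| Visit | Week | Counselling | Peer support | Total of 12 | Share |
|---|---|---|---|---|---|
| FU1 | 2 | 2 | 0–1 | 2–3 | 17–25% |
| FU2 (last CSQ-8) | 4 | 4 | 0–1 | 4–5 | 33–42% |
| FU3 | 6 | 6 | 1–2 | 7–8 | 58–67% |
| FU4 | 13 | 6 | 3–4 | 9–10 | 75–83% |
| FU5 | 26 | 6 | 6 | 12 | 100% |

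After the last CSQ-8 there remain 6 − 4 = 2 counselling sessions and 5–6 peer sessions, or 7–8 of 12 contacts. FU3 is the first visit by which all counselling is scheduled to be complete. FU5 is the first by which the whole package is.

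**4. Can the exit interviews fill the gap?** They involve 10 adolescents and are qualitative. Even if a proportion were read from them, its standard error at p = 0.5 would be √(0.25/10) = 0.158, against the stated upper value of .09.

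**5. Why sessions and not minutes.** The protocol gives two lengths for the counselling sessions: Box 1 has 15–20 minutes for sessions 3–6, while the Design of Study text has 30–45 minutes for each structured session. These must be reconciled. As a sensitivity check, with peer support at 6 × 90 = 540 minutes:
- Box 1 lengths: counselling is 45 + 40 + 4×15 = 145 to 60 + 45 + 4×20 = 185 minutes, so the total is 685–725. By FU2 with no peer session: 115/685 = 16.8% to 145/725 = 20.0%. With one: 205/685 = 29.9% to 235/725 = 32.4%.
- 30–45 minutes for sessions 2–6, with Box 1's length for session 1: counselling is 45 + 5×30 = 195 to 60 + 5×45 = 285 minutes, so the total is 735–825. By FU2 with no peer session: 135/735 = 18.4% to 195/825 = 23.6%. With one: 225/735 = 30.6% to 285/825 = 34.5%.

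The conclusion does not depend on which lengths apply, but the session count is the figure to rely on.

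**The case against.** The strongest reply is that acceptability does not rest on CSQ-8 alone. Table 1 also lists exit interviews as a primary acceptability source, with 10 intervention-arm adolescents and 10 staff, covering ease, usefulness and suggestions. Sessions attended and retention through 6 months would show later disengagement. This stands as a limit on the point. A reader might infer that the pilot cannot describe the acceptability of FB+SP at all, and the protocol does not support that. The gap is in the quantitative score and the proportion built on it.

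The early ratings also have value. By week 4 a participant on schedule has made and revised a safety plan and begun problem-solving, and Box 1 lists sessions 5–6 together with 3–4, with no new component. Calling the early score a rating of a mere introduction would be unfair. Ratings at weeks 2 and 4 also capture people who later leave, which argues for keeping them. Peer support is described as already standard in the adolescent package, so it is not the new element. It is still in Box 1 as part of FB+SP, and almost none of it is rated.

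A reader might also see a flat contradiction in the Design of Study sentence: "Primary and secondary outcomes will be assessed at 2-, 4-, and 6-week; and 3- and 6- month study visits". That is only a weak inconsistency. The sentence lists visits collectively, and other primary outcomes in Table 1 are collected continuously or at exit, so it cannot mean that every primary outcome is measured at every visit.

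Finally, the suicide stigma scale, listed as "Personalized Suicide Stigma Questionnaire^59^ | FU3-5 | Survey", has no baseline, unlike the other scales collected at FU3 to FU5. A reader might infer that it is unusable. It is not: arms can still be compared after randomisation, and the Data Analysis section plans no mediation or change-from-baseline analysis of it. This is a minor, separate matter.

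**Conclusion.** The point holds for the quantitative acceptability score. The last CSQ-8 is taken when at most 4 of 6 counselling sessions and 0–1 of 6 peer sessions are scheduled to have occurred (4–5 of 12, or 33–42%). The planned proportion would describe the early and middle part of counselling, not the full package.

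This rests on three assumptions: on-schedule delivery from enrolment, calendar-month spacing of an undated first peer session, and CSQ-8 as the source of the proportion. Any delay in starting lowers exposure at FU1 and FU2. It would be wrong to say that no peer session can precede FU1, because the first one is not dated.

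The stated precision of .06–.09 is correct for the sample sizes and is not in question.

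**What to change.** In Table 1, keep the adapted CSQ-8 at FU1 and FU2 and add it at FU3 and FU5. Report FU3 as the rating of counselling and FU5 as the rating of the full package. Show the early ratings beside them, with the number responding at each visit. The early ratings should not be replaced: anyone who left between weeks 4 and 6 would then have no CSQ-8 at all, and an FU5 value alone would describe only those retained to 6 months. Reword the Design of Study sentence so that it refers to Table 1 for the timing of each instrument.

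The cost is one short questionnaire at two existing survey visits, with no change to treatment. With no loss to follow-up, the standard error for the 30 intervention participants stays at or below 0.091. Losses by FU5 would widen it, which is a further reason to give the numbers responding. The change is needed before participants pass FU3 and FU5, because missed ratings cannot be recovered.

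Optional and minor: add a baseline assessment to the suicide stigma row, so that a baseline-adjusted comparison is possible. The cost is one extra questionnaire at enrolment.

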Response to suicidal thoughts, ideation or behaviors: For participants who indicate any SIBs during research assessments, IDIs or FGDs, we will follow a suicide risk assessment and response protocol that we have previously deployed in several prior studies in Malawi.^17^ Using this structured protocol, the research assistant will assess suicide risk using the Suicide Risk Assessment Protocol (SRAP) questions.^17^ These questions will allow for differentiation between passive and active suicidal thoughts and assessment of suicide risk factors to further classify active suicidal thoughts into low, medium, or high risk. All participants reporting SIBs will see a clinician that same day. Following the protocol, the research staff will accompany the participant to a clinician with the results of the risk assessment for the clinician to then decide on appropriate further clinical response following the clinic’s standard safety procedures. All clinical staff at the study sites have been trained on suicide risk management, and are able to provide supportive counseling, review a safety plan, provide medication management, and refer to the clinic’s psychiatric nurse as necessary. For acute cases or crises, all clinic staff are trained to refer to the psychiatric unit at Bwaila Hospital in Lilongwe District. Additionally, we will train a study nurse who will be available on-site to assist the existing clinical staff, provide mental health evaluation, brief supportive counseling, information, education and support on SIBs as needed. For acute cases or crises, the study nurse will facilitate referral to the psychiatric unit at Bwaila Hospital. The study nurse will have up to 3 follow-up contacts with all participants reporting SIBs to assess whether they have followed up on recommended referrals or treatment plans and to assess whether any further outreach is needed.

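### Table 1 contradicts the study-visit schedule on the source and timing of the three effectiveness outcomes; if clinic records feed the comparison, suicidality is ascertained differently by arm

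*Protocol*

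**What the plan says.** Table 1 (section 5.6) lists three outcomes under secondary preliminary efficacy, all with the same timing and data type:

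- SIBs: "PHQ-9-A Question 9 and ASQ Tool^50,56^ | Ongoing | Clinic"
- Suicide risk: "Suicide Risk Assessment Protocol^17^ | Ongoing | Clinic"
- Depressive symptoms: "PHQ-9-A^50^ | Ongoing | Clinic"

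The text of section 5.6 describes another route. Under preliminary effectiveness it says "Patients will be surveyed by the RAs at enrollment (baseline), 2 weeks post-enrollment (FU1", and continues through FU5 at 6 months. Abstraction of providers' assessments of depression and SIBs is then introduced as something done in addition. Section 5.1 places primary and secondary outcomes at the study visits at weeks 2, 4 and 6 and months 3 and 6. Section 5.7 analyses efficacy at those same times.

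On contacts outside the study visits, section 5.1 says of FB+SP: "The protocol will include six sessions, starting with the development of the SP during the first session". It adds: "Each of the following sessions will include SIBs and suicide risk assessments". Box 1 puts a SIBs and suicide risk assessment in the first session too. Usual care has an evaluation by a study nurse and up to three follow-up contacts. Clinic staff use the TASR-A for adolescents thought to be at elevated risk.

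**The concern.** The Protocol gives two answers to a basic question: which record supplies the values of SIBs, suicide risk and depressive symptoms that are compared between arms.

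Under one answer, an RA asks both arms the same questions on the same dates. Under the other, the values come from whatever the clinic side recorded. For SIBs and suicide risk the clinic side is not symmetric: only FB+SP has a dated series of assessments, and these are made by the people delivering the treatment. An arm difference could then reflect who was asked, by whom, how often and with which instrument, as well as any treatment effect.

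Reducing SIBs relative to augmented usual care is a stated objective and hypothesis (sections 2.0 and 3.0). Section 5.7 also intends to carry the pilot's standard deviation and intra-cluster correlation into the next trial. Section 5.5 promises cautious interpretation of efficacy, but caution about a small sample does not address a difference in measurement.

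**Working it through.** This is mainly a comparison of passages. The only statistical precision figure in the Protocol, standard errors of .06-.09 for proportions (section 5.5), reproduces as √(p(1−p)/n): at p = 0.5, √(0.25/60) = 0.064 and √(0.25/30) = 0.091. The present point does not touch it.

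**Step 1. Do the Table 1 labels carry meaning?** The table uses *Clinic*, *Survey*, *Study* and *Qual.* as separate data types. Viral load is split into two rows: one ongoing and from the clinic, the other "VL draws | BL, FU5 | Study". Scales collected by survey carry named visits. Read literally, then, the three efficacy rows are not study-collected.

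**Step 2. What does Table 1 leave for the study visits?** At FU1 and FU2 the only survey named is the satisfaction questionnaire. The other repeated scales have follow-up only at FU3-FU5. Among them is the RCADS-25, which touches depression but is listed as a common data element and not as an efficacy outcome. Section 5.7 nevertheless analyses efficacy at weeks 2 and 4. Read literally, Table 1 provides no RA-collected value of the three outcomes for those analyses, or for any other visit.

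**Step 3. What do the other sections provide?** Sections 5.1, 5.6 (text) and 5.7 imply five common follow-up assessments per arm (weeks 2, 4, 6; months 3, 6). The difference in scheduled opportunities is 5 − 5 = 0. Section 6.3 fits this reading: when SIBs are indicated at a research assessment, "the research assistant will assess suicide risk using the Suicide Risk Assessment Protocol (SRAP) questions", in either arm.

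**Step 4. What would clinic-side records provide for SIBs and suicide risk?**

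- *FB+SP:* six dated assessments, one per session in weeks 1-6, made by the counsellor.
- *Usual care:* one nurse evaluation plus 0 to 3 follow-up contacts, so 1 to 4 contacts. None is dated, and the PHQ-9-A, ASQ and SRAP are not named for them. TASR-A use depends on perceived risk.
- *Either arm:* section 6.3 offers up to three nurse contacts to all participants reporting SIBs, so nurse contacts are not confined to usual care.

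Frequency and assessor therefore differ by arm, and the instrument may. Near weeks 2, 4 and 6 an attending FB+SP participant has a session record; a usual-care participant may have none.

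**Step 5. Does this extend to depressive symptoms?** Box 1 names SIBs and suicide risk, not the PHQ-9-A. The six sessions do not show unequal ascertainment of depression. Only the contradiction over source and timing remains.

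**Step 6. Can the bias be sized?** No. More frequent questioning could record more SIBs in FB+SP. Disclosure to one's own counsellor could be higher or lower than to a nurse. Records in usual care that arise because risk looked elevated could over-represent the worst cases there. The Protocol gives no rate for any of these, and they do not all point the same way.

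**The case against.** The strongest reply is that three places in the text agree on common visits and only one table disagrees. Section 5.1 covers secondary outcomes explicitly, and section 5.7 analyses at fixed times. *Ongoing* may mean no more than every visit, and *Clinic* may be loose: Table 1 gives the same labels to feasibility measures such as reasons for non-enrollment, which are not treatment records. No passage says that counselling-session assessments are the outcome data.

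Much of this stands. A reader might infer from Table 1 that ascertainment definitely differs by arm and that the comparison is already biased. The documents do not support that; it follows only if clinic records feed the comparison. A reader might also infer that extra sessions must raise the apparent SIB rate in FB+SP, and size the effect as the chance of at least one positive over several looks. That models a cumulative endpoint. The Protocol compares prevalence at fixed times, so looks do not simply accumulate, and usual care also begins with a nurse evaluation. Nor does section 6.3 show that the suicide-risk outcome is missing for participants who report no SIBs: it describes a safety response, and coding such participants can be left to the SAP.

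What the reply does not remove is the contradiction. The two viral-load rows show that the authors could distinguish clinic from study data when they meant to. A SAP can choose between two recorded sources, but it cannot create visit data that were never collected.

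**Conclusion.** The contradiction is established from the text: Table 1 disagrees with sections 5.1, 5.6 (text) and 5.7 on the source and timing of all three effectiveness outcomes.

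Differential ascertainment is conditional. If Table 1 governs and clinic records enter the comparison, SIBs and suicide risk are measured differently by arm: six counsellor-held assessments in weeks 1-6 against one to four undated nurse contacts plus risk-dependent TASR-A. The direction and size of any resulting bias cannot be derived from the Protocol. The session argument does not cover depressive symptoms.

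This should be fixed, but it is not critical. Efficacy is a secondary aim, and the feasibility, fidelity and acceptability objectives do not depend on it.

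**What to change.** In Table 1, change the three rows so that SIBs, suicide risk and depressive symptoms are RA-administered at baseline and FU1-FU5 in both arms, with a data type that marks them as study-collected. In section 5.7, add one sentence: assessments made in counselling sessions or abstracted from clinic records serve care and safety and do not enter the between-arm comparison.

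The cost is small, because RAs already survey both arms at these visits. If the PHQ-9-A and ASQ are not yet part of the FU1-FU5 interviews, they lengthen them; this needs settling before data are collected. The one analytic downside is that events recorded only between visits are not counted as outcomes. No sample-size figure changes.

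### Suicide stigma is the only one of the 12 repeated survey scales under Covariates & Mediators in Table 1 with no baseline assessment, and no reason is given

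*Protocol*

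**What the plan says.** Table 1 places the suicide stigma scale in the Covariates & Mediators block with this entry: "Personalized Suicide Stigma Questionnaire^59^ | FU3-5 | Survey". The row above it, for HIV stigma, reads "Internalized AIDS-Related Stigma Scale^58^ | BL, FU3-5 | Survey", and the next scale down reads "Suicide Related Coping Scale^60^ | BL, FU3-5 | Survey". The remaining repeated survey scales in the block follow the same baseline-plus-FU3-5 pattern, for example "Adapted Interpersonal Needs Questionnaire items^61^ | BL, FU3-5 | Survey" and "Adapted-Beck Hopelessness Scale items^63,64^ | BL, FU3-5 | Survey".

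The text before the table sets a survey by the research assistants at enrolment and at five follow-ups, with FU3 at 6 weeks, FU4 at 3 months and FU5 at 6 months. Box 1 (Design of Study) places the six individual counselling sessions in weeks 1 to 6. Peer-support groups run monthly for 6 months, and stigma is one of their six topics. Under Target Population, every participant must report current or past suicidal ideation or behaviour. Data Analysis plans a comparison of baseline characteristics between arms. It accounts for baseline values in models of suicidal ideation and behaviour, suicide risk and depressive symptoms, and it names no model for suicide stigma.

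**The concern.** The first suicide stigma value is due at week 6, when the individual sessions are ending, so the schedule yields no value from before randomisation. Four things are lost: change from baseline, use of the scale as a baseline covariate, a check of baseline balance, and baseline adjustment in any arm comparison or mediator model.

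The gap looks unintended. The scale applies to everyone at enrolment, given the eligibility criteria. Sensitive content does not explain it either, because disclosure of suicidality, suicide-related coping and acquired capability for suicide are all asked at baseline. The construct also matters to the trial's own rationale: the Background names stigma around mental illness and suicide as a cause of concealment and a barrier to care.

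The assessment schedule is fixed in the protocol. If the baseline value is not collected, no statistical analysis plan can restore it.

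**Working it through.** **Step 1. Tally of the Assessment Point column in Table 1, survey scales repeated at FU3-5.**

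| Block | Scale | Baseline? |
|---|---|---|
| Covariates & Mediators | HIV stigma | yes |
| | **Suicide stigma** | **no** |
| | Suicide coping | yes |
| | Isolation | yes |
| | Burdensomeness | yes |
| | Hopelessness | yes |
| | Acquired capability | yes |
| | Sleep quality | yes |
| | Trauma | yes |
| | Alcohol/marijuana | yes |
| | Social support | yes |
| | Resilience | yes |
| NIH Common Data Elements | RCADS-25 | yes |
| | DSM-5 cross-cutting | yes |

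Within Covariates & Mediators, 11 of 12 have a baseline. With the two common data elements, it is 13 of 14. The adapted Client Satisfaction Questionnaire-8 (FU1, FU2) also has no baseline, but it is an acceptability outcome about care received and belongs to another block.

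**Step 2. What can be derived for suicide stigma.** Values before randomisation: 0. Change from baseline: not derivable. Change between FU3, FU4 and FU5: derivable. Difference between arms at FU3, FU4 or FU5: derivable.

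**Step 3. Size of the precision loss.** The protocol gives no figure to reproduce here. The one input from it is 30 per arm (Design of Study). The correlation r between baseline and follow-up is an assumption: 0.5, range 0.3 to 0.7. Full retention and equal SDs in the arms are also assumed, and the one degree of freedom spent on adjustment is ignored.

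Standard error of the unadjusted difference in means, in SD units: sqrt(2/30) = 0.258. The same quantity is the SD of a chance difference between arms at baseline, with a 95% range of ±1.96 × 0.258 = ±0.51 SD.

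With adjustment for baseline, the variance is multiplied by 1 − r²:

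| r | 1 − r² | Variance cut | Adjusted SE = 0.258 × sqrt(1 − r²) | Unadjusted total N giving the same precision, 60/(1 − r²) |
|---|---|---|---|---|
| 0.3 | 0.91 | 9% | 0.246 | 66 |
| 0.5 | 0.75 | 25% | 0.224 | 80 |
| 0.7 | 0.51 | 49% | 0.184 | 118 |

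**Step 4. After the fix.** With BL added, the tally becomes 12 of 12 (14 of 14 with the common data elements).

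**The case against.** A reader might infer that the scale is unusable as a mediator, or that it cannot show whether the intervention moved stigma. The protocol does not support either reading. A mediator is measured after randomisation, and suicide stigma at FU3 followed by outcomes at FU4 and FU5 is a usable order. Participants are individually randomised, so the comparison of arms at FU3, FU4 or FU5 is unbiased without a baseline. The ±0.51 SD range for chance imbalance is sampling variation that its standard error already contains. It is not an extra bias.

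A second objection is that the block heading does not make every row a covariate. Some rows are baseline only, and one includes FB+SP appointment dates, which cannot exist before randomisation. This stands: Table 1 does not say which role suicide stigma is to play. It is also true that Data Analysis commits to no model needing its baseline value, that no objective or hypothesis rests on the scale, and that Sample Size Determination treats efficacy as secondary.

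The omission may be deliberate, or it may be an editing slip, since an empty row follows this one in the table. The documents do not settle which. In either case the row needs correcting or explaining.

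These arguments limit the consequences. They do not explain why one scale in 12 departs from the schedule, and they do not replace the missing baseline.

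**Conclusion.** The point holds as a minor inconsistency in the schedule that is cheap to correct. Suicide stigma alone among the 12 repeated survey scales in its block has no baseline, without explanation. That rules out change from baseline, a balance check, use as a baseline covariate and baseline adjustment. It does not bias the randomised comparison at FU3-5 or rule out a mediation analysis.

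The measurable cost is precision. At the assumed r = 0.5, the standard error is 0.258 SD where 0.224 SD was attainable, a 25% difference in variance (9% to 49% for r from 0.3 to 0.7). The tally in Table 1 needs no assumption, whereas the size of the precision loss depends on r, which the protocol does not give. The severity is minor because the scale is exploratory and the trial is a pilot aimed mainly at feasibility, acceptability and fidelity.

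**What to change.** In Table 1, change the assessment point for the Personalized Suicide Stigma Questionnaire from FU3-5 to BL, FU3-5. If the scale serves as a covariate, use only the BL value. If the omission was intended, state the reason in the protocol and say that the scale is not a baseline covariate.

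For participants already enrolled without a baseline value:

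- Keep the between-arm comparison at FU3-5, either unadjusted or with the missing baseline handled in the model.
- Do not use FU3-5 values as ordinary adjustment covariates in treatment-effect models, because they are measured after randomisation and may carry part of the effect.
- A mediation model may still use them as the mediator.

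The cost is a one-line edit to Table 1 and one more questionnaire at the existing baseline survey. The protocol does not give the questionnaire's length, so the added time cannot be stated. The change is best made early, since a baseline value not taken at enrolment cannot be recovered.
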